### Expert and patient involvement

After the detailed intervention protocol is developed, 10–20 experts and patients will be invited to make suggestions regarding the intervention. The researchers will conduct expert consultations by email or face-to-face. According to the professional fields involved, combining the principles of representativeness and authority, the selection criteria for the experts are as follows: (1) are oncologists, breast specialist nurses, clinical dietitians, psychologists, TCM practitioners, chronic disease health management experts, etc.; (2) have 5 years of work experience or more; (3) have an intermediate professional title or above; (4) have a bachelor’s degree or above in the nursing field and a master’s degree or above in medicine or other fields; and (5) volunteer to participate in the consultation and have rich professional knowledge and a rigorous academic attitude. Immediately after the completion of each expert consultation, the intervention protocol will be modified. After the completion of the modification, expert consultation will be conducted until all of the experts have finished. Then, several BC patients will be conveniently sampled after obtaining and reviewing their electronic medical records. We will first obtain their consent and determine their opinions about the intervention by asking questions such as “Can you tell us about your dietary experiences during chemotherapy? And “What changes or difficulties have you had with your diet since starting chemotherapy?” In parallel, patients will be invited to a multidisciplinary meeting to share their thoughts and participate in developing their management intervention content. After the intervention is modified, we will conduct a pilot study to assess the participation burden and duration. Based on the feedback and performance, the final intervention for which we plan to implement during the RCT will be identified. Patients will also be encouraged to recommend the intervention to the public or other patients.

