### Study design

A prospective 8-week, two-arm, single-center, single-blinded parallel-group RCT with a pretest and follow-up will be conducted by an MDT. Female patients who are diagnosed with BC and waiting to start chemotherapy or who are in the early or middle stage of chemotherapy will be randomized to receive either usual dietary care or the multidisciplinary early dietary management intervention. The participants in the intervention group will receive the multidisciplinary early intervention measures constructed based on the ITHBC. In contrast, the control group will receive only the usual cancer dietary care education at admission and education manuals based on the Dietary Guidelines for Chinese Residents, the World or American Guidelines, etc. The intervention consists of the following eight themes, with sessions provide once per week: adverse reaction coping, dietary information and habit regulation, self-care self-efficacy training, treatment self-regulation training, dietary supplement and TCM use, social support seeking, weight management, and outcome expectation education. Detailed information is provided in Fig. 1. Eight intervention sessions will be provided throughout admission for chemotherapy and a home-based interval chemotherapy period. This intervention will be initiated during the early and middle stages of chemotherapy. Standard chemotherapy cycles include 4, 6, and 8 cycles. For example, for patients receiving 4 chemotherapy cycles, the first intervention session will be provided during the first or second admission for chemotherapy. For patients receiving 6 cycles, the first intervention session will be provided during the first, second, third, or fourth admission. For patients receiving 8 cycles, the first intervention session will be provided during the first, second, third, fourth, fifth or sixth admission. The duration of intervention sessions during different chemotherapy cycles is shown in Fig. 2. In addition to the baseline measurements, follow-up measurements were taken immediately after the end of the intervention (T_1_) and at 1 (T_2_), 3 (T_3_), 6 (T_4_) and 12 months (T_5_) after the intervention. T_1_ was measured immediately after the end of the eighth intervention session. T_2_, T_3_, T_4_ and T_5_ will be measured 30, 90, 180 and 360 days after the T_1_ measurement date, respectively. The intervention process is shown in Fig. 3. The same time points for follow-up in the intervention group will be also used for the control group.

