### Recruitment and procedures

The potential participants will be enrolled from a tertiary-level general hospital in Shaanxi, China. The hospital is an essential medical resource in Northwest China, and the affiliated hospital of a well-known medical university with a profound history and accumulation in China. It has a large cancer center and provides continuous care from the inpatient to home-based interval chemotherapy periods for more than 3000 BC patients annually. We will contact participants in two main ways, the first being through active contact. Second, posters will be placed in waiting rooms and examination rooms at the oncology department or breast surgery department of this hospital, advertisements will be posted on the department’s official website, WeChat public account, video platform, etc., or word of mouth will be used. Interested women will be asked to contact research members via phone, email, or WeChat for detailed information. Regarding the second approach, researchers will learn about potential participants who meet the requirements through recommendations from health care staff in the department. After obtaining informed consent, the research team members will obtain the patients’ names and numbers, contact the patients to introduce the specific purpose and process of this study, and then ask them about their willingness to participate.

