### Blinding

This is a multidisciplinary intervention on dietary management for BC patients, and the BC patients and intervention providers will know the group assignments. Because three face-to-face training sessions for MDT members will be conducted before the intervention is implemented and patients need to receive eight diet-related health education sessions, blinding patients and intervention providers may be challenging. Thus, a single-blinded design will be used, in which the statisticians who analyze the data are not aware of the group assignments.

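### The protocol encourages patients to recommend the intervention without saying who, to whom or when; done before follow-up ends, this may expose controls and dilute the between-group difference

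*Protocol article*

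**What the plan says.** The sentence at issue is the last one under Expert and patient involvement: "Patients will also be encouraged to recommend the intervention to the public or other patients". It sets no time limit and does not name the patients concerned.

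The text around it is about development. Experts are consulted, and "Then, several BC patients will be conveniently sampled after obtaining and reviewing their electronic medical records". A pilot follows, and the sentence directly before the one at issue reads "Based on the feedback and performance, the final intervention for which we plan to implement during the RCT will be identified".

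Other sections describe the setting:

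- **Study design:** "A prospective 8-week, two-arm, single-center, single-blinded parallel-group RCT with a pretest and follow-up will be conducted by an MDT". Of the comparator it says that "the control group will receive only the usual cancer dietary care education at admission", and it adds written manuals.
- **Blinding:** "the BC patients and intervention providers will know the group assignments". The masking is confined to the analysis: "Thus, a single-blinded design will be used, in which the statisticians who analyze the data are not aware of the group assignments".
- **Randomization:** 88 patients are to be enrolled over 3 months and allocated individually, 1:1.
- **Implementation of the multidisciplinary early intervention:** part of the content goes out electronically, through WeChat, online video and electronic handouts.
- **Primary outcome:** the DMBQ is reported by the patient and has domains on information acquisition, coping with adverse reactions and regulation of dietary habits.
- **Sample size:** the only allowance is for 20% loss to follow-up.

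**The concern.** The two arms share one hospital and overlap in time, and patients know which arm they are in. Some of the content can be passed on by telephone or message. Several DMBQ items concern finding dietary information and acting on it, so a control could answer differently after receiving advice or materials from another patient without attending any session.

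An instruction that encourages recommendation to other patients, with no end date and no exception for controls, therefore opens a route to contamination that the trial does not need. Exposed controls would tend to move towards the intervention arm, and the estimated difference would move towards zero. The stated sample size has no margin for this.

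The objection is to something the article positively states. It is not an objection that an article omits operational safeguards, which may well stand in the full protocol.

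**Working it through.** **1. What the sentence fixes.**

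| Question | Answer in the text |
|---|---|
| Who recommends? | Patients; consulted, pilot or randomised is not stated |
| To whom? | Anyone, including other patients; centre not stated, controls not excluded |
| When? | Not stated |

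There are three possible readings:

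- *Randomised patients during the trial:* controls may receive advice or materials.
- *Consulted or pilot patients before or during recruitment:* people who later enter either arm may already know the programme. Recruitment and procedures also lists word of mouth as a recruitment route ("or word of mouth will be used"). That acts before allocation and is not in itself evidence of contamination.
- *Dissemination after the trial:* harmless, but the text does not say so.

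**2. The plan's own figure.** The stated inputs are effect size 0.25, power 0.95, α 0.05 and total 72 (36 per group) before loss to follow-up. With two groups these inputs give 210 for a one-way ANOVA. With six measurements and an assumed correlation of 0.5, they give 124 for the between-group test and 28 for the group-by-time interaction. A total of 72 appears only under settings the article does not state, for example the between-group test with six measurements and a correlation of 0.2. That is a separate matter. Here it means only that the 95% starting point has to be taken as nominal.

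**3. Dilution.** Let c be the share of controls exposed and u the fraction of the full effect that each of them gains. The difference is multiplied by (1 − c·u), and the sample size needed for unchanged power by 1/(1 − c·u)². Both c and u are assumptions. Setting u = 1 gives the largest loss at each c.

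Taking 72 as giving exactly 95% power (two-sided α 0.05, one degree of freedom, normal approximation):

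power = Φ[(1.960 + 1.645)(1 − c) − 1.960]

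| c (u = 1) | Effect multiplier | Φ argument | Power | N factor | Total N to keep 95% |
|---|---|---|---|---|---|
| 0 | 1.0 | 1.645 | 95% | 1.00 | 72 |
| 10% | 0.9 | 3.605 × 0.9 − 1.960 = 1.28 | 90% | 1.23 | 89 |
| 20% | 0.8 | 3.605 × 0.8 − 1.960 = 0.92 | 82% | 1.56 | 113 |
| 30% | 0.7 | 3.605 × 0.7 − 1.960 = 0.56 | 71% | 2.04 | 147 |

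Totals are before loss to follow-up. A two-sample t test calibrated to 95% power at 36 per arm gives 0.901, 0.822 and 0.713, which agrees.

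Partial uptake shrinks the loss. If 20% of controls each gained half the effect, c·u = 0.10 and power would be 90%, as in the 10% row.

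**4. Length of a deferral.** Recruitment of 3 months (about 91 days), 8 weeks of intervention (56 days) and T5 at 360 days after T1 give 91 + 56 + 360 = 507 days. That is about 17 months from the start of recruitment to the last T5, if the last patient starts the sessions promptly.

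**The case against.** The strongest reply is context. The sentence ends a section on development and piloting, straight after the statement that the final intervention will be settled. The nearest patients are those consulted or piloted, so it may be no more than a patient-involvement or dissemination remark. A reader might infer that randomised intervention patients are told to promote the programme to controls in the same hospital. The text does not say that. It names neither randomised patients nor the centre, and the hospital treats more than 3000 breast cancer patients a year against 44 controls.

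Second, recommending is not delivering. The intervention is eight weekly sessions of 1.5–2 hours led by the team, two of them face to face and others live online. Some of the forwardable material points to public sources, and controls already receive guideline-based lectures, manuals and help on request between admissions. Full uptake by an exposed control is therefore unlikely.

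Third, the direction is not certain. Controls who hear praise for a programme they were not allocated might report worse, which would widen the difference. But that arises from the open allocation itself, and removing this sentence would not cure it.

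These replies limit the size and forbid a definite claim of dilution. They do not remove the point. The sentence as written permits the harmful reading, and nothing in it confines the activity to a harmless time.

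**Conclusion.** The point holds as a possible and avoidable source of contamination. As worded, the encouragement may reach current or future controls while follow-up is running, in a single-centre trial that is open to patients and has a self-reported primary outcome, and it may dilute the difference. It cannot be concluded that the effect will be diluted, or that controls of the centre are the intended audience.

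The size is unknown. The fall from a nominal 95% to about 90%, 82% or 71% rests on assumed exposure of 10%, 20% or 30%, on full uptake by each exposed control, and on a 95% baseline that the stated inputs do not reproduce without further settings. At each rate it is an upper bound on the loss from dilution. The case for acting is that the change is almost free and that the trial gains nothing from promotion during follow-up.

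**What to change.** Delete the sentence, or reword it to say who may recommend the programme and that this starts only after the last patient's T5 assessment. Ask intervention patients not to forward session materials until then.

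The cost is publicity delayed until about 17 months after recruitment starts, and one added instruction to the intervention group. Sample size and analysis need not change on this account.

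Optionally, ask controls at the final assessment only whether they saw or received programme material. Asked earlier, the item could itself draw attention to the material. Asked at the end, it would give a rough measure of exposure to report beside the main result.

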### Outcome and measurements

We determined the intervention outcomes based on the theoretical guidance of the ITHBC, which states that patients’ knowledge and beliefs, self-regulation, and social support may influence their health behavior (proximal outcome) and health status (distal outcome). The primary outcome of this intervention is dietary management behavior. The secondary outcomes are psychological and physiological health status. The effect of the intervention will be compared with that of the control, both as a primary and secondary outcome. Each indicator is an independent metric.

### Primary outcome

**Dietary management behavior.** The patient-reported Dietary Management Behavior Questionnaire (DMBQ) will be used to assess dietary management behavior in BC patients treated with chemotherapy. Our group members previously developed this questionnaire in 2023 based on the theoretical guidance of the ITHBC and the Capacity, Opportunity, Motivation-Behavior Model (COM-B) [33]. After conducting a scoping review to construct an item pool, three rounds of a multicenter survey were completed, including item selection and evaluation of the reliability, validation, and discriminative ability of the formal verified version. This tool comprises 4 domains and 22 items, including the adverse reaction coping (4 items), dietary information acquisition (5 items), dietary habit regulation (8 items), nutritional supplements, and dietary replacement (5 items) domains. The items are rated on a 5-point Likert scale ranging from ‘strongly disagree’ (1 point) to ‘strongly agree’ (5 points), with higher scores indicating better DMB. The structure was tested among 760 Chinese BC patients treated with chemotherapy from three hospitals. The total cumulative variance contribution rate of the 4 domains and the 22-item questionnaire was 62.67%, the Cronbach’s α coefficient was 0.908, the split-half reliability coefficient was 0.833, and the test-retest reliability coefficient was 0.938. Moreover, there were significant differences in the average scores of each dimension among patients with different ages, education levels, BMIs, menopausal statuses, and histological stages (all *P* < 0.05), and these differences were reflected in different pairwise comparison groups, indicating good reliability, validation and discriminative ability in BC populations.

### Secondary outcomes

#### Self-care self-efficacy

The ‘Strategies Used by People to Promote Health (SUPPH)’ assessment tool will be used to evaluate BC patients’ self-care self-efficacy. The self-reported SUPPH has been widely used among chronic disease patients. It was translated into Chinese and introduced in China by Huijuan Qian in 2011 [34] and was verified among cancer patients. The Chinese version includes 3 domains and 28 items, including the positive attitude (15 items), stress reduction (10 items), and decision making (3 items) domains. The items are rated on a 5-point Likert scale ranging from ‘very little confidence’ (1 point) to ‘very confident’ (5 points), with higher scores indicating greater confidence in health self-management. The three domains’ split-half reliability coefficients and the Chinese version’s overall scale were 0.80 ~ 0.94, and the Cronbach’s α coefficient was 0.85 ~ 0.97.

#### Quality of life

We will adopt the Chinese version of the Functional Assessment of Cancer Therapy-Breast (FACT-B, version 4) introduced by Chonghua Wan [35] in 2002 to measure BC patients’ quality of life. This self-reported instrument has been widely used worldwide, with 5 domains and 36 items, including the physical well-being (PWB, 7 items), social/family well-being (SWB, 7 items), emotional well-being (EWB, 6 items), functional well-being (FWB, 7 items) and additional concerns (AC, 9 items) domains. The items are rated on 5-point Likert scale ranging from ‘not at all’ (0 points) to ‘very much’ (4 points), with higher scores indicating a better quality of life. The test-retest reliability of the five domains from the Chinese version, namely, the PWB, SWB, EWB, FWB, and AC domains, and the overall scale was 0.82 ~ 0.89, and the Cronbach’s α coefficient for the five domains was 0.61 ~ 0.84.

### Other outcomes

#### Demographic and clinical information

Self-designed demographic and clinical factor questionnaires will be used to collect this information. To ensure the representativeness and comprehensiveness of the demographic and clinical factors of BC patients as much as possible, we referred to guidelines and previous literature related to diet, nutrition, lifestyle, and self-health management in BC patients treated with chemotherapy. After discussion among the research team members, the questionnaire will be used to collect demographic (age, BMI, marital status, number of children, educational level, per capita monthly household income, living conditions, work status, and menopausal status) and clinical information (time of diagnosis, unilateral or bilateral BC status, cancer stage and chemotherapy type).

#### BMI

To minimize bias, we will provide each patient with an electronic weighing scale of the same make, model, and batch. The patients will be told to perform measurements in the morning after defecation and urination, wearing only underwear. Considering the limitations of the patients’ ages and educational levels as well as to improve operability, direct input of data by the patients will be avoided. Patients will be asked to weigh themselves at 7–8 am, and the data will be uploaded to their bound app and sent to the researchers via a screenshot. Screenshots of each measurement for each patient will then be recorded, checked by two researchers, entered into statistical software, and automatically saved in the cloud. The screenshot will show the specific date, time, and weight value. Height will be recorded after being measured using the hospital’s anthropometer at the patient’s initial admission. BMI will be calculated directly by using the formula in the statistical software.

#### Adherence to the intervention

The MDT members will track and summarize patient personnel participation at the end of each week’s intervention session. Each participant’s adherence to the intervention will be defined as the number of times the participant attends a complete session compared to the number of prescribed sessions, including completing the assigned tasks and actively interacting with MDT members to provide feedback. Specifically, we defined the nonadherence criteria as (1) being late or leaving early (more than one hour) during the intervention; (2) failing to complete the assigned task more than 3 times; (3) no communication or interaction with MDT members for more than half a month; (4) failing to follow up more than 3 times; and (5) being absent during more than 2 sessions.

### Data collection

Two other professionally trained researchers will collect the data with a statistical professional. Printed questionnaires will be distributed to participants face-to-face at baseline (T_0_). The questionnaires will be distributed and collected on the spot, and the members will check for missing or unclear information. In addition, an electronic questionnaire collection platform will be used immediately (T_1_) and 1 month (T_2_), 3 months (T_3_), 6 months (T4) and 12 months (T_5_) after the intervention. An answer will be required for each item. According to the preliminary pilot test, the average completion time is approximately 10–20 min. The completion time will be recorded in the background of the system. Patients who take less than 6 min or more than 30 min will be asked to complete the questionnaire again or excluded if the questionnaire is invalid. Patients will receive a reward of RMB 300 if they complete all assessments promptly. At each measurement, the entire questionnaire will include the demographic and clinical information questionnaires, the DMBQ, the Chinese version of the SUPPH and FACT-B, and BMI measurement.

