### Statistical analysis

We will use IBM SPSS Statistics 21.0 software to analyze the statistical data. Descriptive statistics, such as the number of patients with different ages, education levels, cancer stages and types of chemotherapy, as well as the percentage of patients in different groups relative to the total number of patients, will be calculated for different groups of demographic and clinical information. The mean and standard deviation will be used to compare the DMBQ total and dimensions scores, the SUPPH and FACT-B scores, and BMI. To compare the baseline balance between the two groups, two independent sample *t* tests, chi-square tests or Mann‒Whitney U tests, will be used, depending on whether the data distribution satisfies homogeneity of variance. The Shapiro‒Wilk test will be used to verify whether the scores of the two groups at different time points follow a normal distribution. If the data are balanced, repeated ANOVA will be adopted. Otherwise, we will use a generalized estimating equation (GEE) to analyze the intervention’s time, group, and interaction effects [36]. For all the above tests, *P* < 0.05 will indicate a statistically significant difference, the α level will be 0.05, and the tests will be two-sided. We will use intention-to-treat (ITT) analysis to minimize bias for sensitivity analysis [37]. The results of the last measurement of the patients who drop out of the study will be taken as the effect, which assumes that they complete the intervention, and the analysis will be reconducted with the GEE. Furthermore, missing data will be imputed with the mean values of the characteristics or with the help of multiple imputation methods if they are random and unrelated to the research elements.

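### Completion-time rule acts after randomisation and, as worded, can exclude randomised patients on an undefined validity criterion

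*Protocol article*

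**What the plan says.** The rule is in the Data collection section of the protocol article: "Patients who take less than 6 min or more than 30 min will be asked to complete the questionnaire again or excluded". The closing words of that sentence limit exclusion to a questionnaire that is invalid. The plan therefore has two outcomes for a form outside the time limits: a repeat, or exclusion if the form is invalid.

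The same section fixes when the rule can operate. At baseline, "Printed questionnaires will be distributed to participants face-to-face at baseline", and staff check the forms on the spot. The electronic platform serves T1 to T5, and of that platform the article says "The completion time will be recorded in the background of the system". The reference point for the limits is a pilot: "According to the preliminary pilot test, the average completion time is approximately 10–20 min". Each measurement includes the DMBQ, SUPPH and FACT-B.

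The Statistical analysis section says "We will use intention-to-treat (ITT) analysis to minimize bias for sensitivity analysis". It carries the last measurement forward for patients who drop out. It allows mean or multiple imputation where the missing data are random and unconnected with what is being studied. It does not mention forms or patients removed because of completion time.

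**The concern.** A rule that acts only on follow-up forms removes outcome data after randomisation, on the basis of something the patient did after allocation. If the patients removed differ in outcome from those kept, and the removal differs between arms in amount or in kind, the group comparison is no longer protected by randomisation.

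The link to outcome is an inference, but the article supports it. The Primary outcome section reports that DMBQ dimension scores differ significantly by age and education. The BMI section avoids direct data entry by patients because of their ages and educational levels. The Background describes nausea and fatigue during chemotherapy. All of these could plausibly slow a patient filling in a long electronic form.

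The rule also leaves room for judgement. Invalid is not defined, nothing says when a repeat is requested and when exclusion follows, and nothing says which answers count after a repeat. Blinding is stated only for the statisticians who analyse the data. Whoever judges a form invalid is not said to be unaware of the arm or of the answers.

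**Working it through.** The plan gives no figure for this rule, so there is none to reproduce. The check is a reading of the text followed by arithmetic on assumed rates.

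**1. When the rule acts.** Baseline is on paper. Timing is described only for the electronic system, which is used at T1 to T5. All five of those visits follow randomisation.

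**2. What is removed.** The grammatical subject of the sentence is the patient, while the validity condition attaches to the questionnaire. Two readings result:
- Patient excluded: all of that patient's data leave the analysis.
- Form voided: one visit is missing. Even so, the article's first-choice analysis is repeated ANOVA, which in its standard form uses only patients with every time point. One voided form that is not imputed would then drop the patient. GEE, the alternative, would keep the remaining visits.

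**3. Whether the Statistical analysis section restores the data.** Carry-forward is written for drop-outs and belongs to the sensitivity analysis. Imputation carries a condition that removal for completion time does not clearly meet. Neither clearly covers these cases.

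**4. What the limits mean.** Items: 22 (DMBQ) + 28 (SUPPH) + 36 (FACT-B) = 86, plus demographic and clinical questions.
- Lower limit: 6 × 60 / 86 = 4.2 seconds per item at most.
- Upper limit: 30 × 60 / 86 = 20.9 seconds per item at most.
- Pilot average of 10 to 20 minutes: 7.0 to 14.0 seconds per item at most.

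The lower limit looks like an ordinary screen for careless answers. The upper limit is 1.5 times the top of the pilot average (30 / 20) and could more easily catch a slow but genuine respondent.

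**5. How many patients could be flagged (assumed rates).** Let p be the share of forms flagged per visit, over five visits. With independent flags, the share of patients flagged at least once is 1 − (1 − p)^5. If the same patients are flagged every time, it is p.

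| p per visit (assumed) | Independent flags | Same patients each time |
|---|---|---|
| 2% | 9.6% | 2% |
| 5% | 22.6% | 5% |
| 10% | 41.0% | 10% |

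Illness, age or education as the cause would make the same patients slow repeatedly, which points towards the right-hand column. These are flags, not exclusions: a repeat may be accepted.

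**6. Possible bias (assumed rates and correlation).** Suppose a share q of an arm is excluded from the low end of a normal propensity that correlates r with the outcome. The arm mean then rises by r × φ(z_q) / (1 − q) standard deviations. Before multiplying by r, the factor is 0.109 for q = 5%, 0.195 for q = 10% and 0.350 for q = 20%. The shift in the group difference is r times the gap between the factors:

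| Excluded, arm A / arm B | r = 0.3 | r = 0.5 |
|---|---|---|
| 5% / 5% | 0.00 | 0.00 |
| 5% / 10% | 0.03 | 0.04 |
| 5% / 20% | 0.07 | 0.12 |

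The direction depends on which arm loses more patients and on whether those lost score low or high.

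**The case against.** The strongest defence is that this is a routine quality check. A form finished at about 4 seconds per item is probably not a considered answer, a repeat keeps the patient in the trial, and exclusion applies only if the form is invalid. The sentence can be read as voiding the form rather than removing the patient, and a condensed article may leave the definition of invalid to a fuller document. Most of this stands: flagging is sound, a repeat is defensible, and forcing every implausibly fast first form into the primary analysis would be debatable. What it does not answer is that the published sentence makes patients the ones excluded, and that it does so after randomisation.

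A reader might infer four stronger points that the documents do not support:
- *Every patient outside the limits is removed.* The text offers a repeat and conditions exclusion on validity.
- *The rule uses up the 20% allowance for loss to follow-up.* That requires every flagged patient to be excluded, no repeat to be accepted, and a flag rate that the article does not give.
- *Intervention patients answer faster because they know the content.* Nothing in the article shows this. Both arms complete the questionnaires at the same time points, so practice with the forms would affect both.
- *The rule contradicts a primary intention-to-treat analysis.* The article assigns intention-to-treat to the sensitivity analysis and does not claim it for the primary one.

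**Conclusion.** The point holds in a limited form. The article states a rule that acts on follow-up forms carrying the primary outcome, rests on an undefined criterion, and as worded allows randomised patients to be excluded. Because completion time plausibly relates to symptoms, age and education, and DMBQ scores are reported to differ by age and education, such exclusions can bias the comparison.

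The size is unknown. No flag, repeat or exclusion rate is given, and there is no evidence that rates would differ by arm. The shifts of 0.03 to 0.12 SD rest on assumed unequal exclusion (5% against 10% to 20%) and assumed correlations of 0.3 to 0.5. With equal exclusion and equal selection the difference does not move. The case for change is that the wording is easily corrected in advance, whereas answers discarded or overwritten may not be recoverable.

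**What to change.** State the following before the data are analysed:

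1. No randomised patient is excluded from the primary analysis because of completion time.
2. A time under 6 or over 30 minutes is a quality flag on that form only.
3. If a repeat is requested, both the first and the repeat answers are kept. Which set is used is fixed in advance by a rule applied without knowledge of arm.
4. A form is voided only on a written criterion applied blind to arm. A voided form counts as a missing visit under the planned missing-data method.
5. One sensitivity analysis omits the flagged forms. The numbers flagged, repeated and voided are reported by arm.

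The cost is a few sentences in the plan, storage of both sets of answers and one extra analysis. The downside is slightly more measurement noise from flagged forms that stay in the primary analysis.
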